## Abstract

**Background:**

Following Spinal Cord Injury (SCI), 53% of people develop neuropathic pain (NP). NP can be more debilitating than other consequences of SCI, and a persistent health issue. Pharmacotherapies are commonly recommended for NP management in SCI, although severe pain often remains refractory to these treatments in many sufferers. Furthermore, poor medication adherence exists, stemming from unacceptable side-effects and fear of dependency.

Sensorimotor stimulation using active walking with robotic assistance has not been well studied in NP after SCI, despite convincing locomotor-based pre-clinical studies, identifying prevention and reversal of NP.

Our primary aim is to assess the impact of exoskeleton-based walking on NP intensity and interference after SCI and examine feasibility outcomes for progression to a definitive trial.

**Methods:**

This is a phase 2 single-blinded, randomised feasibility study. It will test the feasibility and acceptability of exoskeleton-based walking 3 times per week for 12 weeks (intervention), as a mechanistic-based intervention for NP after SCI. The comparator will be an equally dosed, blended relaxation programme devoid of motor imagery prompts. 40 participants with moderate-to-severe NP post SCI will be recruited and randomised to intervention and comparator groups.

The primary outcomes are feasibility outcomes for progression to definitive trial which include recruitment and retention rates, adverse events and acceptability of the intervention.

Secondary outcomes explore changes in NP intensity and interference as measured by the International Spinal Cord Injury Pain Basic Data Set 3.0 (ISCIPBDS) at baseline, post-intervention (week 13) and at 6-month follow-up.

**Conclusions:**

There is a need to explore non-pharmacological management of NP after SCI. The findings of this feasibility trial will inform the development of a future multicentre, international RCT,

**Trial Registration:**

NCT06463418, 08/07/2024,
https://clinicaltrials.gov/study/NCT06463418.

## Introduction

### Background and rationale

Traumatic spinal cord injury (SCI) incidence in Ireland is 11.5-13.3 per million per year (
Smith *et al.*, 2018), placing it as a rare condition. However, the SCI itself in many cases results in significant physical disability and poses a considerable functional and economic burden at an individual and societal level (
McDaid *et al.*, 2019). Pain (nociceptive and neuropathic) is frequently experienced after SCI. Neuropathic pain (NP) type, commonly subdivided into at-level and below level pain, is the most distressing. Following SCI, approximately 53% of people develop neuropathic pain (NP) (
Burke *et al.*, 2017;
Finnerup *et al.*, 2014). National SCI data identify high pain intensity and pain interference levels with NP presentations and significantly poorer quality of life (QoL) when compared with other pain phenotypes (
Burke *et al.*, 2018;
Burke *et al.*, 2019). Individuals have described NP as more debilitating than the other consequences of SCI (
Hearn *et al.*, 2015), as their most persistent health issue and adequate pain relief as an unmet need (
Kennedy *et al.*, 2006). The mainstay of NP treatment after SCI is pharmacotherapy (
Loh *et al.*, 2022). Pregabalin/gabapentin, duloxetine, amitriptyline and/or opioids are the first- and second-line treatments recommended (
Loh *et al.*, 2022), with high use of non-steroidal anti-inflammatories and paracetamol also reported in survey data (
Burke *et al.*, 2019;
Cardenas & Jensen, 2006;
Jensen *et al.*, 2005). Severe pain remains refractory to these treatments in 2⁄3 sufferers (
Guy *et al.*, 2016) and significant, often intolerable, central nervous system side-effects are reported (
Siddall *et al.*, 2006). These, together with fear of medication dependency, result in poor adherence to pharmacological regimens leading to a call for non-pharmacological treatment options for people with NP after SCI (
Cardenas & Jensen, 2006;
Löfgren & Norrbrink, 2012;
Siddall *et al.*, 2006;
Widerström-Noga *et al.*, 2020).

The intensity of the NP may increase over time after SCI to become a chronic and life-long condition (
Finnerup *et al.*, 2014;
Siddall, 2009). NP following SCI that emerges within the first year after SCI and tends to become chronic is characterised by sensory deficits, spontaneous or stimulus-evoked pain, including allodynia and hyperalgesia and may be associated with dysesthesia and paraesthesia. Qualitative studies, exploring people’s experiences with NP in daily life after SCI (
Buscemi *et al.*, 2018;
Widerström-Noga *et al.*, 2017) emphasise the difficult nature of pain, its treatment resistance, and its deleterious effects on QoL. They further identify the need to gain more knowledge and skills in relation to self-management and coping with pain to reduce its impact on their daily life (
Henwood *et al.*, 2012;
Norrbrink & Löfgren, 2016). The need for better information regarding pain and additional treatment options has been highlighted in the literature by people with SCI, calling for a stronger focus on persistent pain as a consequence of SCI, better access to healthcare providers with expertise in this area (
Norman *et al.*, 2010). International data identify the proportional burden of NP following SCI as significant. Ninety-four percent of individuals with SCI NP are prescribed >1 medication, the mean number of physician office visits in a 6-month period due to SCI NP is reported as 2 and the total annualised cost of NP per subject in the United States (US) is reported as $26,270 (direct $8,636, indirect $17,634) (
Mann *et al.*, 2013). The presence of pain is further associated with lower return to work rates following injury, and more than a third of individuals with SCI in employment report frequent pain interference with their work (
Widerström-Noga *et al.*, 2001). Pain interference with function, health status and work are noted to be significantly worse in individuals with more severe NP (P<0.0005), where overall work impairment is reported at 38% (
Widerström-Noga *et al.*, 2001).

NP after SCI is multi-faceted and heterogenous, making isolation of specific mechanisms more challenging. Nonetheless, proposed mechanisms include neuronal hyperexcitability (central and peripheral sensitisation) and corticothalamic maladaptive neuroplasticity (
Finnerup *et al.*, 2009). Additionally, NP symptom severity post SCI has been reported to be associated with a combination of residual spinothalamic tract (STT) function below the level of injury and with catastrophising pain coping mechanisms (
Widerström-Noga *et al.*, 2016). Our understanding of the mechanistic effects of sensorimotor stimulation on NP in SCI stem from Phantom Limb Pain research where significant reversal of cortical dysfunction in the primary somatosensory cortex is evident (
Foell *et al.*, 2014). Similar maladaptive cortical reorganisation is hypothesised to be associated with NP in SCI (
Flor, 2008;
Wrigley *et al.*, 2009), supported by data garnered from electroencephalography (EEG) studies identifying thalamo-cortical dysrhythmia (
Boord *et al.*, 2008;
Jensen *et al.*, 2013;
Sarnthein & Jeanmonod, 2008;
Vuckovic *et al.*, 2018a) and decreased reactivity in alpha band power signals to eye opening (
Boord *et al.*, 2008;
Vuckovic *et al.*, 2014). Thus, EEG may have application as a biomarker both for current NP and as a predictor of NP development in SCI (
Mussigmann *et al.*, 2022;
Vuckovic *et al.*, 2018b).

Virtual reality (immersive virtual walking/virtual illusion/imagined walking) has shown promise for reducing NP intensity and interference after SCI (
Austin & Siddall, 2021;
Gustin *et al.*, 2023;
Trost *et al.*, 2022). Virtual illusion interventions show evidence of direct and corrective stimulation to maladaptive sensorimotor reorganisation in SCI patients with NP (
Eick & Richardson, 2015;
Moseley, 2007), supporting the theory that NP mechanisms are reversible. However, actual sensorimotor intervention studies are inconclusive in SCI at this point (
Nees *et al.*, 2017) with limited focus on walking despite compelling preclinical studies showing prevention and /or reversal of SCI neuropathic pain (
Dugan & Sagen, 2015;
Dugan *et al.*, 2021;
Hutchinson *et al.*, 2004). Notably in these animal studies, other exercise modalities such as swimming and stance training had short term or no effect on NP after SCI. This is suggestive of the fact that the characteristics of walking not seen in swimming and stance training, namely the rhythmic stimulation of proprioceptive and mechanosensory afferents combined with weight bearing might be the potential mechanisms that are driving this reduction in NP (
Dugan *et al.*, 2021).

Robotic-assisted gait training after SCI is well established in the neurorehabilitation space, notably for motor impairment and gait outcomes in incomplete SCI (
Alashram *et al.*, 2021;
Stampacchia *et al.*, 2022). However, its mechanistic effects on NP for individuals with SCI have not been well investigated to date. Only two case studies/series employing robotic-assisted gait were identified in the extant literature that mandated participants have NP in the moderate and severe categories prior to using the exoskeleton and results demonstrated meaningful reductions in pain intensity ratings (
Cruciger *et al.*, 2016;
Kressler *et al.*, 2014). The ExSCIP randomised feasibility trial addresses the current lack of clinical trials in this area, examining exoskeleton-based walking 3 times per week, as a mechanistic-based intervention for NP after SCI. It will test the feasibility and acceptability of an exoskeleton-based walking intervention, and whether it demonstrates positive signals in reduction of NP intensity and interference levels to warrant onward progression to a definitive trial.

### Aims and objectives

The overall aim of this study is to examine the feasibility and acceptability of an exoskeleton, mechanistic-targeted, walking intervention for NP in people with SCI.

The primary objectives for the study are:

1. Implement an exoskeleton training programme for people with below level NP > 6 months after a traumatic SCI.2. Pilot and assess the impact of an exoskeleton-based walking intervention in NP > 6 months after SCI, examining feasibility outcomes and short and long-term (6-months) changes in pain intensity and pain interference.

## Methods

### Study design and setting

The ExSCIP study is a single centre, phase 2 randomised, single blinded, feasibility trial, informed by Bowen’s framework for feasibility studies (
Bowen *et al.*, 2009). Given SCI is considered a rare condition, we will apply a randomised feasibility study to allow a better-informed decision on whether to proceed to a larger multi-centre and international trial (
Eldridge *et al.*, 2016). This trial protocol has been registered on clinicaltrials.gov (NCT06463418)
https://clinicaltrials.gov/study/NCT06463418)

Progression criteria are based on consideration of the primary objectives around feasibility and the potential for effectiveness and implementation in clinical practice. Quantitative and qualitative process evaluation data will be analysed to consider the following continuation criteria.

Successful uptake, recruitment, and retention.Successful implementation of the ExSCIP intervention.Process evaluation indicates that ExSCIP is acceptable to people with NP after SCI and to staff delivering the intervention.A positive effect on pain and pain interference outcomes are identified and are meaningful.

The intervention will be delivered in the Motion Analysis Laboratory at University College Dublin (UCD).

### Participants

Participants will be adults who have sustained a traumatic SCI with confirmed below-level NP. Participants will be recruited from the Spinal Injuries Ireland (SII) national support service via information leaflet and trial advertisement and the outpatient SCI clinic at the National Rehabilitation Hospital (NRH) via advertisement fliers and posters. Interested parties will contact the researcher directly to proceed to the next stage of assessment/screening for the trial as outlined below. Eligibility criteria for participants can be found in
Table 1.

**Table 1. T1:** Participant Eligibility Criteria.

Inclusion Criteria	Exclusion Criteria
Individuals aged 18 years and older	Individuals aged < 18 years old
Confirmed traumatic SCI of > 6 months duration with complete or incomplete paraplegia or tetraplegia. This must be confirmed by registration at the National Spinal Cord System of Care Programme.	Non-traumatic SCI, cauda equina lesions (excluding fracture at L1/2 causing paraplegia) or Guillain Barré diagnoses.
Below-level NP (≥ 3 levels below neurological level and/or extending to at-level region) starting after the SCI, persisting for >3 continuous months, despite pharmacotherapy ( Bryce *et al.*, 2012) matching the ISCIP Pain Classification and confirmed by neurological examination, and a score of ≥4 on the Douleur Neuropathique 4 (DN4) Bouhassira *et al.*, 2005).	Nociceptive pain profiles only based on subjective pain history and clinical examination.
Moderate to severe NP levels, confirmed as pain ≥ 3 (moderate) and ≥ 6 (severe) on the 0-10 Numerical Rating Scale (NRS) for NP (averaged over a week) included in the ISCIPBDS 3.0 ( Widerström-Noga *et al.*, 2023).	NP intensities of <3 (0-10 NRS)
Exoskeleton naïve.	Anthropometric measurements incompatible with the exoskeleton device (i.e. height >1.9m, weight >100kgs, significant lower limb spasticity).
Stable pain and spasticity medication regimen (i.e. no medication changes for ≥3 months).	Unstable comorbid medical condition/ psychiatric condition/medication regimen.
Have the capacity to provide informed consent.	Planned surgery coinciding with the intervention.
	Pregnancy.
	Substance use disorders.

### Below-level neuropathic pain screening protocol

**
*Stage 1: Telephone screening*
**

NP will be screened for as a minimum criterion initially by phone. This phone screening will do the following:

- Confirm their SCI diagnosis (e.g. traumatic aetiology and >6 months post injury).- Confirm they are on a stable medication regimen.- Confirm they are exoskeleton naïve.- Screen for the presence and location of NP supported by the use of the Spinal Cord Injury Pain Instrument (SCIPI) (
Bryce *et al.*, 2014). Score of ≥ 2 is indicative of probable NP in SCI. (Permission has been obtained for reuse of this instrument).- Screen for anthropometric exclusion criteria.- Once the phone screening has been completed, candidates deemed to be potentially suitable to participate pending an in-person assessment. Potential participants will be provided with a participant information leaflet at this point and given a minimum one-week grace period to provide informed consent agreeing to undergoing an in-person assessment and to participate in the study.

**
*Stage 2: In-Person assessment*
**

Once informed consent is obtained from candidates, an in-person assessment will be performed by an independent assessor. The assessment will entail the following steps:

**Confirmation of presence of moderate to severe below level NP:**

- NP will be confirmed based on a neurological examination, a score of ≥4 on the Douleur Neuropathique 4 (DN4) (
Bouhassira *et al.*, 2005) and a comprehensive pain history. (Permission has been obtained for reuse of this instrument).- This will be supported using the ISCIP Pain Classification (
Bryce *et al.*, 2012).- Moderate and severe NP as confirmed above will be described as pain ≥ 3 and ≥ 6 on the 0-10 Numerical Rating Scale (NRS) for NP (averaged over a week). (Permission has been obtained for reuse of this instrument).

**Anthropometric and clinical assessment for compatibility for use of exoskeleton:**

- Participants will undergo an anthropometric and clinical assessment to ensure no height, weight, joint range of movement or muscle spasticity restrictions to exoskeleton use apply.

**
*Stage 3: Data collection*
**

- The independent assessor will collect baseline data for candidates who meet inclusion criteria for the following:◦ Social and health demographics (gender, age, years since injury, neurological level of injury, ASIA impairment scale)◦ Full ISCIPBDS 3.0 for NP intensity and interference measures (
Widerström-Noga *et al.*, 2023). (Permission has been obtained for reuse of this instrument).◦ Neuropathic Pain Symptom Inventory (NPSI) (
Bouhassira *et al.*, 2004;
Wong *et al.*, 2020). (Permission has been obtained for reuse of this instrument).◦ EQ-5D-5L (
Herdman *et al.*, 2011) (Permission has been obtained for reuse of this instrument).◦ Resting EEG recordings will be recorded with the participants eyes open for 3 minutes and eyes closed for 3 minutes (NeuroCONCISE device), with participants seated in a dimly lit room shielded from sound and stray electric.
Figure 1 details the flow of participants during the course of the study.

- For full details of data collection and management procedures a data management plan for the study has been published (
https://dmp.ucd.ie/public_plans)

**Figure 1. f1:**
[figure not shown]
Participant flow through study.

### Sample size, randomisation, and blinding

As ExSCIP is a feasibility trial, a sample size calculation will not be conducted. The trial aims to recruit 20 participants to the intervention arm and 20 to the control arm, retaining at least 32 at follow-up. Due to practical considerations including traumatic SCI being a rare condition in Ireland, the strict eligibility criteria in addition to the precedent set by previous RCT’s in this area with considerably smaller sample sizes (
Martinez *et al.*, 2018), this number is considered adequate to inform whether sufficient participants can be recruited and retained in the study and to evaluate the feasibility goals outlined.

Following informed consent and baseline evaluation for exoskeleton, recruited participants will then be randomly allocated to the intervention group (ExSCIP) or to the comparator group (receiving a blended relaxation programme devoid of motor imagery). This will be completed by an independent gatekeeper based in the UCD Centre for Support and Training in Analysis and Research (CSTAR), using a pre-generated electronic randomisation schedule stratified by NP severity. Allocation disclosure will be made by telephone by the independent gatekeeper in CSTAR to the trial interventionist after informed consent and baseline evaluation.

To minimise potential biases, all assessments and outcome measures (baseline, post intervention and 6-month follow-up) will be taken by an independent assessor blinded to the treatment allocation. The data analyst will also be blinded to the intervention allocation.

Blinding participants to the ExSCIP intervention is not feasible. The hypothesis of the study will be masked however in the information to subjects. Participants will be informed that the trial is comparing two types of treatment, to avoid higher expectations in the ExSCIP group.

### Description of intervention and comparator

Participants will be randomised to either:

**Intervention (ExSCIP) group:** the intervention group will complete an exoskeleton-based, mechanistic-targeted, progressive walking programme consisting of one-hour sessions of robotic walking 3 times a week for 12 weeks with hands-on supervision provided by a trained, CORU-registered physiotherapist in the UCD Motion Analysis Laboratory. Those randomised to the intervention group will undergo an initial familiarisation trial walking session in the device under the direct supervision of the PI, to optimise device settings to each individual.

Rest periods will be allowed as required and, as individual aerobic capacity will differ, the programme will be individually tailored to increase the number of steps taken and the number of consecutive steps taken without rest during progressive sessions. Total steps taken and the number of overall scheduled sessions attended will be recorded.

**Control group:** the control group will complete an equally dosed blended relaxation programme, devoid of any motor imagery prompts. It will comprise one face-to-face relaxation class per week alongside 2 online classes over a 12-week period.

Participants in both groups will be permitted to continue with their usual care regimen throughout the duration of the trial. They will not be permitted to participate in additional exoskeleton interventions outside of those provided as part of this study.

### Outcomes

**
*Primary outcomes*
**

The primary outcomes will focus on trial feasibility. Full details of these and progression criteria to a multicentre, international RCT can be found in
Table 2:

**Table 2. T2:** Feasibility Outcomes and Progression Criteria.

Feasibility Outcomes	Progression Criteria
Number of individuals who contact researchers about the trial.	Successful intervention uptake, with recruitment rates of ≥35% of individuals deemed eligible following in-person assessment and at least 20 individuals randomised to the two arms.
Recruitment rates disaggregated by SII and NRH channels (recruitment capacity at named sites).	Loss to follow-up/attrition rates < 20%.
Number of individuals screened by phone.	Qualitative data that indicates that ExSCIP is an acceptable intervention to individuals with NP following SCI and to physiotherapists delivering the intervention, where no insurmountable barriers were identified.
Number of individuals who are eligible to proceed to in person-assessment following phone screening.	Safe implementation of the ExSCIP intervention: no serious adverse events
Number of individuals who consent to participate in the study following phone screening.	Average programme adherence of ≥ 80% of all sessions.
Trial uptake rates.	A non-inferior effect for NP intensity is observed in the intervention arm in comparison to the control arm.
Number who are eligible to participate in the study after in-person assessment.	A Minimal Clinically Important Difference (MCID) for NP intensity in an SCI population (1.74 points decrease on NRS) is observed within the 95% confidence interval for mean change for the intervention arm ( Farrar *et al*., 2001).
Number randomised to participate in the study.	
Adherence with the 12-week exoskeleton walking programme (attendance and total number of steps taken)	
Any safety/adverse events.	
Feasibility of stratified randomisation	
Number who are lost to follow up at week 13 and 6-month follow up.	
Feasibility of assessment procedures.	
Time needed to collect and analyse data.	

**
*Secondary outcomes*
**

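### The 35% recruitment rate in Table 2 is taken among people who have already consented, so refusal cannot lower it and it does not measure uptake

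*Protocol article*

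**What the plan says.** The order of events is set out in three places in the protocol article.

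- **Consent, after phone screening.** In Stage 1 of the below-level neuropathic pain screening protocol, candidates who pass the phone screen receive the information leaflet and are "given a minimum one-week grace period to provide informed consent agreeing to undergoing an in-person assessment and to participate in the study".
- **In-person assessment, after consent.** Stage 2 opens: "Once informed consent is obtained from candidates, an in-person assessment will be performed by an independent assessor".
- **Baseline data, then randomisation.** In Stage 3, "The independent assessor will collect baseline data for candidates who meet inclusion criteria". The section on sample size, randomisation and blinding continues: "Following informed consent and baseline evaluation for exoskeleton, recruited participants will then be randomly allocated". No second consent or decision step is described between confirmed eligibility and allocation.

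Table 2 (Outcomes) then defines successful uptake by two joint conditions: "recruitment rates of ≥35% of individuals deemed eligible following in-person assessment" and "at least 20 individuals randomised to the two arms". Its list of feasibility outcomes also includes contacts, phone screens, people eligible after the phone screen, "Number of individuals who consent to participate in the study following phone screening", uptake rates (not further defined), people eligible after the in-person assessment, and people randomised. None of the stages before consent carries a percentage threshold. The article gives no derivation for 35%.

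**The concern.** A recruitment rate used to decide on a larger trial should show how many of the people who could join are willing to. Here the denominator is formed after that decision has been made. Those who read the leaflet and decline leave the trial between the phone screen and consent, so they appear in neither the numerator nor the denominator.

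Recruitment is a named primary outcome in the abstract, and uptake, recruitment and retention form the first continuation criterion under Study design and setting. The sample size section stresses that traumatic spinal cord injury is rare in Ireland and that eligibility is strict, so the number of suitable people needed per participant is a central unknown for a multicentre trial. If the only percentage attached to uptake cannot respond to refusal, a value near 100% could be read as strong uptake when it shows only that people who had agreed to join went on to be randomised.

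**Working it through.** **Inputs from the protocol article.** Threshold 35%; denominator, people eligible after the in-person assessment (Table 2). Planned sample 20 + 20 = 40 (sample size section). Minimum number randomised 20 (Table 2). As 35% has no stated derivation, there is no figure to reproduce; the check is how the threshold behaves.

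**Step 1. What it takes to fail.** With R randomised and E eligible in person, the rate is R/E, and the largest E that still passes is the whole-number part of R/0.35.

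| R | R/0.35 | Largest E that passes | Smallest E that fails | Losses needed to fail |
|---|---|---|---|---|
| 40 | 114.3 | 114 (40/114 = 35.1%) | 115 (40/115 = 34.8%) | 115 − 40 = 75 |
| 20 | 57.1 | 57 (20/57 = 35.1%) | 58 (20/58 = 34.5%) | 58 − 20 = 38 |

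Every one of those lost would be a person who had consented and been found eligible.

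**Step 2. What the rate adds to the count.** If at least 20 are randomised and E is 57 or fewer, the rate is at least 20/57 = 35.1%. The 35% condition is then met automatically, and it can bind only when 58 or more people are eligible in person. If the 20 is meant per arm (the wording allows either reading), the same holds up to E = 114.

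**Step 3. Chance that the rate passes.** Let p be the share of consented, eligible people who go on to randomisation. The article does not give p, so a range is assumed. The exact binomial probability of reaching 35%, ignoring the count condition, is:

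| Assumed p | E = 40 (pass = 14 or more) | E = 57 (pass = 20 or more) |
|---|---|---|
| 0.5 | 98.1% | 99.2% |
| 0.6 | 99.96% | 99.996% |
| 0.7 or higher | above 99.999% | above 99.999% |

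A p of 0.5 would be pessimistic for people who have just agreed to take part.

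**Step 4. Sensitivity to refusal.** Assumptions, none from the article: 80% of those consenting are eligible in person, and 90% of those are randomised. Randomised over phone-eligible is then consent share × 0.8 × 0.9.

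| Consenting / phone-eligible (assumed) | Randomised / phone-eligible | Table 2 rate (randomised / eligible in person) |
|---|---|---|
| 20% | 14% | 90% |
| 30% | 22% | 90% |
| 40% | 29% | 90% |
| 50% | 36% | 90% |
| 70% | 50% | 90% |

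The first two columns move with willingness to join. The Table 2 rate does not.

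**The case against.** **The criterion has a second half, and it can fail.** A reader might infer that the whole uptake criterion is met by construction. The article does not support that. At least 20 people must also be randomised, and if most suitable people decline, that number may not be reached. Poor willingness can therefore block progression through the count. This stands, and it confines the defect to the 35% rate. A count still does not show how many suitable people are needed per participant.

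**Refusal is recorded.** A reader might also infer that refusals are hidden from the progression decision. They are not: Table 2 collects the phone-eligible and consenting numbers, and Study design and setting says that process data will inform the continuation criteria. This stands too. What is missing is a threshold on that step.

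**No pre-consent denominator is perfect.** Under Participants, interested people contact the researcher themselves, so the phone-eligible are already volunteers, and those who saw an advertisement and did not respond remain uncounted. In addition, randomised over phone-eligible mixes refusal with ineligibility found at the in-person assessment. Both points are fair. The second is why consenting over phone-eligible is the better measure of uptake, with randomised over phone-eligible serving only as overall yield.

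**The wording could mean that 35% of some wider group is found eligible.** That is not the plain reading, and it would measure eligibility yield, which does not match the label of uptake either.

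**Conclusion.** The point holds for the 35% rate. Its denominator contains only people who have consented to participate, so refusal cannot lower it. It fails only if at least 75 consented, eligible people are lost before randomisation with 40 randomised, or at least 38 with 20 randomised. This rests on the sequence in the screening protocol and on there being no further decision step before allocation, as the article describes it. The loss figures need no assumption about patient flow; the pass probabilities and the refusal table do, and they are illustrations over a range.

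It does not follow that 35% is the right value for a pre-consent rate, since the article does not justify it for any denominator.

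The rate should be fixed, because it is a stated decision threshold that does not measure what its label claims. It does not affect participant safety, allocation or any effect estimate, and the informative rates can be calculated from counts already collected. It is therefore not a flaw that undermines the trial.

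**What to change.** In Table 2:

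1. Define the uptake rate as number consenting divided by number eligible to proceed after phone screening.
2. Report number randomised divided by number eligible after phone screening as overall yield.
3. Set and justify a threshold for the new uptake rate, without carrying 35% over by default. Do this in a dated amendment before the recruitment data are reviewed.
4. Keep the condition of at least 20 randomised, and state whether it is a total or a number per arm.
5. Report number randomised divided by number eligible in person only as a conversion step, without the uptake label.

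No new data are needed, since Table 2 already lists every count. The cost is a dated, justified amendment to a trial that the article describes as ongoing, and a reported rate that will probably look less favourable.
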